### Study device

The tDCS device supplies current at a constant strength. The Sooma tDCS, manufactured by Sooma Oy, Helsinki, Finland will be used to deliver the direct current stimulation. As part of this system, two electrode cups with hydrogel stimulation pads inserted will be used to deliver the current. Pads will be soaked in 15 ml saline solution causing it to expand and form a soft and uniform stimulation surface. The neoprene cap will be used to keep the electrodes in place. The device is designed for at-home treatment, offering ease of use and portability (please refer to tDCS setup and stimulation section for information about the safe use of the device). The treatments can be self-administered by the participant/legal guardian/carer at home, under the remote supervision of a medical professional.

### Strategies to improve adherence to the intervention

Adherence to the intervention is facilitated by close monitoring of the participant by the study team. If patients receive treatment at home, they will be monitored remotely.

### Withdrawal and relevant concomitant care permitted during the study

Standard care for participants continues throughout the study. No intervention is prohibited. Participants have the right to withdraw from the study at any time without having to give a reason. The investigator may withdraw a participant from the study at any time if the investigator considers it necessary. As per consent, if participants are withdrawn from the study, the information already obtained will be kept. Patients will be able to continue their regular treatment. If they wish, patients will be able to continue their (daily) tDCS treatment according to the study treatment plan, even if they withdraw from the study. In that case, no further study data will be collected after withdrawal.

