Participants aged 16 years or over with the capacity to provide consent, will be consented as adults and asked to complete their own informed consent form. For participants aged under 16 years, consent will be obtained on behalf of the participant from their parent or a person with parental responsibility. Where appropriate, written assent will be obtained from the child. If a participant has their 16th birthday whilst participating in the study, they will be re-consented as an adult. If they lack capacity to provide consent, a consultee will be asked to provide a consultee declaration on the participant’s behalf. Additional consent includes permission to obtain information from medical records (until six months after study end), to obtain accelerometer data, and to obtain optional short video recordings. No biological specimens will be collected.

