#### Target difference and sample size

Assuming a minimum of one assessment per patient event per day, each event will contribute 14 data points over 14 days of treatment (tDCS or sham). Further assuming no association between days of treatment and reduction in epilepsy events, the outcome data are treated as clustered data for the purposes of the power calculation. Assuming 5% type I error, 90% power, and 10% intra-patient correlation, 28 patient events will be required over 14 days of treatment to detect an improvement of 20% in events that achieved 50% reduction in seizure frequency. The sample size calculation also assumes that only 10% of the events in the placebo group will achieve 50% reduction in epilepsy frequency from baseline (on day 0). To account for drop-out, 30 patient events will be required for this study. The patient events will be allocated equally to active and sham tDCS groups. These calculations were determined based on clinical significance, patient perspectives, historical data, statistical considerations, and regulatory guidelines [25].

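### Withdrawal ends all study data collection even when the patient stays on study-plan tDCS, so later outcomes and new adverse events are lost without the participant having refused them

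*Protocol article*

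**What the plan says.** The Protocol article's section on withdrawal and concomitant care gives two ways out of the study. The participant may leave at any time without a reason, and "The investigator may withdraw a participant from the study at any time if the investigator considers it necessary". What was gathered before that point is retained: "if participants are withdrawn from the study, the information already obtained will be kept". The section then provides that, should they want to, "patients will be able to continue their (daily) tDCS treatment according to the study treatment plan, even if they withdraw from the study". The next sentence reads: "In that case, no further study data will be collected after withdrawal".

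Four other sections bear on this:

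- **Consent** lists permissions item by item: "Additional consent includes permission to obtain information from medical records (until six months after study end"), and also accelerometer data and optional video.
- **Post-intervention** plans an EEG on the day after the last intervention day and six months of data from the medical record. It does not say whether withdrawn patients are included.
- **Adverse event (AE) reporting and harms** makes events that arise during tDCS, or result from it, reportable. They are followed until they resolve or stabilise, and serious events go to the sponsor within 24 hours.
- **Statistical analyses** makes a GEE on the binary 50% reduction the primary analysis. It announces a sensitivity analysis for missing data without giving the method.

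**The concern.** This is a written rule, not a detail left for later. An analysis plan can choose how to handle missing data, but it cannot recover data that the protocol says not to collect.

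Two things are at stake.

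**Primary comparison.** A GEE without weighting is generally valid only when missingness is unrelated to the outcome. Lack of improvement is a plausible reason to leave, and leaving does not cost the patient the treatment. The trial plans only 30 events, so each one counts.

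**Harms.** A withdrawn patient who continues tDCS has the same off-label exposure as one who stays. Discontinuation due to adverse events is a secondary endpoint, and there is no data monitoring committee; the article relies instead on regular review of safety and efficacy. Such review needs the data to be collected.

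**Working it through.** **1. The plan's own sample size.** The inputs are in the section on target difference and sample size. Control response: "only 10% of the events in the placebo group will achieve 50% reduction in epilepsy frequency from baseline". Active response is 20 points higher, so 30%. Cluster size: "each event will contribute 14 data points over 14 days of treatment (tDCS or sham"). Result: "Assuming 5% type I error, 90% power, and 10% intra-patient correlation, 28 patient events will be required over 14 days of treatment".

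- Independent observations per arm (two-sided 5%, no continuity correction): n = [1.960·√(2·0.20·0.80) + 1.282·√(0.10·0.90 + 0.30·0.70)]² / 0.20² = 82.
- Design effect: 1 + (14 − 1)·0.10 = 2.3.
- Events per arm: 82·2.3/14 = 13.47, rounded up to 14, so 28 in total. This matches the plan, although the plan does not state whether the test is one- or two-sided.
- Drop-out allowance: 30 − 28 = 2 events, or 2/30 = 6.7%.

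**2. Precision.** On the same model, power by number of the 30 events lost entirely is 92.9% (0 lost), 91.1% (2), 90.1% (3), 89.0% (4), 86.4% (6) and 83.2% (8). Precision is not the main issue.

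**3. Bias when available days are kept.** No withdrawal rate or reason is documented, so everything in this step is an assumption. The set-up was:

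- 40,000 events per arm over 14 days, with daily response probability drawn from a beta distribution with mean 0.30 or 0.10 and the stated intra-event correlation (ICC).
- After each non-response day, withdrawal with probability 0.01 or 0.03; none after a response day.
- All observed days pooled with equal weight (independence working correlation).

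Difference in percentage points (true value 20.0):

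| ICC | Daily withdrawal probability | None | Sham arm only | Both arms | Early-start arm only |
|---|---|---|---|---|---|
| 0.10 | 0.01 | 19.9 | 20.0 | 20.2 | 20.2 |
| 0.10 | 0.03 | 19.9 | 20.0 | 20.0 | 20.5 |
| 0.5 | 0.01 | 19.8 | 19.8 | 20.5 | 20.8 |
| 0.5 | 0.03 | 19.8 | 19.2 | 21.2 | 22.1 |
| 0.8 | 0.01 | 19.7 | 19.4 | 20.4 | 20.9 |
| 0.8 | 0.03 | 19.7 | 18.3 | 22.0 | 23.4 |

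A daily probability of 0.01 gives 9–12% of events withdrawn in an affected arm; 0.03 gives 25–32%. The runs without withdrawal returned 19.7 to 19.9, so a few tenths of a point are simulation noise. Like the sample-size model, this holds 30% versus 10% over all 14 days, whereas the arms differ only on days 1 and 2 and treatment can end early on resolution.

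**4. Extreme case: whole events vanish from one arm.** With 15 events per arm, expected responders are 4.5 and 1.5.

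- Two early-start non-responders lost: 4.5/13 − 10% = 34.6% − 10% = 24.6 points. Three lost: 4.5/12 − 10% = 27.5 points.
- Two sham non-responders lost: 30% − 1.5/13 = 30% − 11.5% = 18.5 points. Three lost: 30% − 1.5/12 = 17.5 points.

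**5. Adverse events, side by side.** The harms section makes new events on tDCS reportable. The withdrawal section stops study data for a patient who is still on tDCS. Nothing says which prevails.

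**The case against.** The strongest reply is that this is the ordinary consequence of leaving a study: the person may keep the treatment but is no longer studied. Several parts of that case stand.

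- **Investigator withdrawal.** A reader might infer that the rule plainly covers it. The sentence refers back to the patient's own wish to continue after the patient's own withdrawal, so the text is only ambiguous here. It gives no separate rule for investigator withdrawals.
- **Denominator.** A reader might infer that non-responders drop out of the comparison altogether. They do not: data already obtained are kept, and an event withdrawn on day 6 still contributes its earlier days. The 24.6 and 27.5 points in step 4 require whole non-responding events to vanish from one arm, which nothing in the article supports.
- **Randomised contrast.** Both arms receive active tDCS from day 3, so later withdrawal leaves the sham-controlled window observed. Blinding makes arm-specific withdrawal less likely.
- **Monitoring.** A reader might infer that device exposure goes unmonitored. The article ends study data, not care. Home tDCS is under remote medical supervision, standard care continues, and adverse events already reported are followed to resolution or stabilisation.
- **Documents not shown.** The missing-data method belongs in the analysis plan, and the consent form may say more.

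The rule itself remains. Someone content to be followed has no stated way to leave the study and still contribute data.

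**Conclusion.** The point holds in a limited form. The article stops study data at withdrawal even while study-plan tDCS continues, does not distinguish leaving from refusing data, and is unclear for withdrawal by the investigator. The lost outcomes can bias the primary GEE if withdrawal is related to response, in either direction and by an unknown amount.

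Under the assumptions in step 3 the shift is about 1 point or less at 9–12% withdrawal, which already exceeds the 6.7% allowance. At the planned ICC of 0.10 it stays small even at 25–32%. Shifts of roughly 2 to 3 points appear only at that heavier withdrawal combined with an ICC of 0.5 or 0.8; anything larger needs whole events lost from one arm. The documents do not support calling the primary comparison biased, only open to bias that could be avoided.

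The safety part is narrower still: new adverse events on continued tDCS have no stated route into study data, in tension with the harms section. The change is worth making because it is cheap and lost outcomes cannot be recovered afterwards.

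**What to change.** In the withdrawal section, separate (a) leaving the study or being withdrawn by the investigator from (b) refusing further data collection. In case (a), unless the participant or guardian refuses, continue what is already planned: the seizure diary, adverse event recording, end-of-study EEG and six-month record review. Analyse the event in its randomised arm. In case (b), stop collection and keep what was obtained. Record the date and reason for each withdrawal.

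Reconcile the withdrawal, Post-intervention and Adverse event reporting sections so that they agree on which data are collected from a withdrawn patient who is still receiving tDCS. Whether treatment continues is a clinical matter and is not touched here.

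The cost is one protocol paragraph, one option on the consent form if it is not already there, and a little more follow-up work. The required 28 events and the target of 30 do not change.

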### Provisions for post-study care

Standard care will continue within the UK National Health Service (NHS) during and after the study.

### Intervention allocation

The experimental unit for this study will be a single patient episode (rather than the patient) identified by an event ID, since one patient can have two or more separate episodes of focal *status epilepticus* over the course of the study. Participant event/episode IDs will be randomly assigned to groups in a 1:1 ratio using block randomisation (6 blocks) by the sealed envelope software [26]. Based on the event ID the dedicated team member will be able to infer the study arm that determines the device setup for the first two days, i.e. active (early start) vs. sham (delayed start).

TDCS device marked as #1 will be set up individually for each experimental event for day 1 & 2 to either sham or active treatment with the aid of a special tool and instructional video. A second device marked as #2 will permanently be set up for active treatment and used for the remaining sessions (3 up to 14). One member of the team, not involved in the delivery of tDCS or data analysis, will be responsible for the randomization process, and sham/active device assignment and delivery. The random group assignment will be kept secret in a password protected file only accessible to the responsible team member. All remaining team members and all participants and relatives will be unaware to which treatment arm the participant is assigned. A record will be kept confirming when and by whom the randomisation code was requested and provided.

### Blinding

The study team, as well as the participant, parents, carers, and any consultee, will be blinded to the randomisation (double blinding). The team member who sets the randomisation will not be involved in any other study-related activities.

Block randomisation prevents accidental unblinding affecting the blinding of remaining study events. Unblinding at the end of study will happen after the statistical analysis plan is finalised. Early withdrawal based on adverse events (AE) may require unblinding.

## Assessment and collection of outcomes

### Pre-intervention screening

Following informed consent, participants will undergo the following screening assessments to confirm eligibility for the study:

Collection of basic demographic information (name, address, date of birth, NHS number).Collection of full medical history.Physical examination and vital signs (height, weight, heart rate, respiration rate, blood pressure and head circumference).Baseline seizure frequency assessment through seizure diary and video assessment on day 0.

These assessments will be documented in the participant’s hospital records.

### Intervention period

Participants who are confirmed to be suitable for continued participation in the study will then undergo the following assessments/activities:

Randomisation.tDCS for a period of 20 min once a day, for a period of up to 14 days.Completion of a seizure diary/collection of seizure events daily over the tDCS treatment period.1–2 min of daily video recordings of areas of the body affected by seizures (if consented).Continuous accelerometery measurements (in consented).

### Post-intervention

Following the tDCS treatment period, participants will undergo the following assessment:

End of study EEG (obtained the day after the last intervention day).Further follow up through regular clinical care. For six months data will be collected from the patient’s medical record.

Unless the study is prematurely discontinued, the end of the study will be the date of the last visit of the last participant and/or the completion of all follow-up monitoring.

## Data management and confidentiality

### Data collection tools and source documentation identification

Completed study consent forms will be held in the Investigator Site File. Copies will be held in the participant medical records. Source data for this study will consist of annotations in the participant medical records, patient diaries, video recordings, accelerometery data, and data from EEG and MRI exams. Completed researcher/clinician assessment tools will be stored in the Investigator Site File.

Participants will be identified on any assessment tools via their unique study ID number rather than by name. Data will be transcribed from the source data directly onto the study database. Participants and study events will be identified on the database via the unique study ID number (i.e., the study database will be classed as containing pseudonymised data only).

As part of the study, short videos (1–2 min) of participants’ areas of the body affected by their seizures will be captured (either in clinic or by parents/carers at the home). These videos will be transferred onto secure NHS servers and pseudonymised (i.e. by blurring out facial features) prior to transfer onto Newcastle University systems for long-term storage/analysis. Measures will be taken to ensure that the identifiable images (i.e. prior to pseudonymization) are transferred securely. Participants will be provided with information about how the data from these videos will be managed and stored as part of the informed consent process. This is an optional assessment; participants will be advised of this during recruitment and of the fact that they can still participate in the study without video capture.

All efforts will be made to ensure that the data provided in the source documents is as complete as possible. Regular review of data completeness and regular data cleaning activities will be undertaken. These activities may include telephoning participants to obtain missing information. Any activities which involve contacting study participants will be conducted by delegated members of the site team who are known to the participant (i.e. study research nurse).

### Data handling and record keeping

The study will comply with all relevant data protection laws. Data entry will be performed by a member of the research team at the site. The study database will include Excel spreadsheets and files in .csv format (for EEG) and DICOM format (for MRI) which will be read with other appropriate software approved by the Sponsor. The database will be held on secure servers within Newcastle University. Access to the area of the server containing the study database will be restricted to research team members only. Permission to access the study database will be issued by the Chief Investigator. The link between each participant unique study ID number and their name will be via the study recruitment log, which will be held in the Investigator Site File (ISF), an electronic version of this log may also be held securely on NHS computer systems.

The ISF will be held in a secure area within Newcastle Hospitals with access restricted to the study team only. Following completion of the study, fully anonymised sets of raw data may be made available for 3rd party research purposes with the appropriate data transfer procedures.

### Access to data and dissemination of results

Direct access to study data including source data contained in the participant medical notes and personal identifiable data contained in the ISF will be granted to authorised representatives of the Sponsor, Newcastle University or regulatory authorities for the purposes of monitoring, audit or inspection. Consent for this will be obtained from participants during recruitment.

Study participants will be advised in the participant information sheet that they can contact the study team to request a summary of the research results once the study is completed. The results of this study will be disseminated via peer-reviewed scientific journals, conference presentations and other publications.

### Archiving

Archiving will be authorised by the study sponsor following submission of the end-of-study reports to the REC and funder. Essential documents will be archived for a period defined by the study sponsor and archiving will be according to sponsor processes and procedures. Destruction of essential documents following the required period of archiving will require sponsor authorisation. Pseudonymised study data held on the study database will be retained on Newcastle University servers for 20 years following the end of study and used for further analysis. Long term storage of data will be in accordance with the Newcastle Joint Research Office policy for archiving using the approved archiving facility. Arrangements to ensure data security will be in accordance with NuTH Trust policies and procedures.

## Statistical methods

### Statistical analyses

The data will be tabulated using descriptive statistics. Mean and standard deviation will be reported for continuous data. Median and range will also be reported for skewed data. Categorical data will be described using percentages and frequencies.

The primary analysis of the binary outcome of a 50% reduction in epilepsy frequency (number and duration of seizures, jerks/min) from baseline (counted on day 0) will be completed by applying a generalised estimating equation to thus obtain robust standard errors and test whether the tDCS group improves more rapidly than the sham group.

Further analysis will consider a more complex model incorporating random slopes where appropriate. Sensitivity analysis for missing data will also be investigated. Other outcome data will be analysed as appropriate using a mixed effects model for continuous data and a generalised estimating equation for binary, categorical or count data with appropriate distribution and link function.

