### Recruitment

This study will involve the assessment of at least 30 episodes of focal *status epilepticus* in participants with a genetically confirmed diagnosis of mitochondrial disease. This will either equate to the recruitment of 30 inpatient participants each presenting with one episode of focal *status epilepticus*, or fewer than 30 participants with individual participants contributing more than one episode of focal *status epilepticus* (provided each event per participant has a different focal location). If participants participate multiple times, they will be re-consented for each new focal event. If participants recruited into the study were already to be inpatients due to an acute episode of focal *status epilepticus* that cannot be resolved with antiepileptic drugs they will remain as such for the duration of their participation.

We host the largest UK mitochondrial disease patient cohort with over 1800 patients. Each patient on this cohort has actively consented to participate in research. This cohort has facilitated our robust feasibility assessment to establish that the time to target patient recruitment is attainable in the proposed timeline.

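### The primary test relies on GEE robust standard errors with at most 30 events and names no small-sample method; a plain robust z test would not deliver the 5% level.

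*Protocol article*

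**What the plan says.** The Statistical analyses section of the protocol article fixes the primary analysis of the binary outcome (a 50% reduction from day 0) as "applying a generalised estimating equation to thus obtain robust standard errors" and sets the aim to "test whether the tDCS group improves more rapidly than the sham group". It names no small-sample correction, reference distribution, link for the primary model, cluster unit or time window.

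The number of clusters comes from the section on target difference and sample size: "Assuming 5% type I error, 90% power, and 10% intra-patient correlation, 28 patient events will be required over 14 days of treatment", raised to 30 for drop-out and split equally between arms. That section also assumes that "each event will contribute 14 data points over 14 days of treatment (tDCS or sham") and that "only 10% of the events in the placebo group will achieve 50% reduction in epilepsy frequency", and it is powered "to detect an improvement of 20% in events that achieved 50% reduction in seizure frequency".

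Under Intervention allocation, "The experimental unit for this study will be a single patient episode (rather than the patient"). Under Recruitment, the 30 events may come from "fewer than 30 participants with individual participants contributing more than one episode of focal" status epilepticus. The randomisation and intervention section limits sham to days 1 and 2, with all participants on active stimulation from day 3.

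**The concern.** The robust (sandwich) variance is justified by a large number of independent clusters. With 15 per arm, the residuals are pulled towards the fitted arm means, so the variance is estimated too low, and a normal reference ignores the uncertainty in that estimate. Both make the test reject too often. A low response rate adds a second difficulty when few days are used: an arm may have no responder, and a log odds ratio is then infinite.

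The p-value and interval of the primary result are at stake. In a rare disease this trial is unlikely to be repeated soon, so a nominal 5% that is really 7% or 8%, or a primary model that returns no estimate, would weaken the conclusion.

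**Working it through.** **Reproducing the planned size.** Inputs: 10% vs 30%, two-sided 5% (sidedness is not stated; two-sided reproduces the figure), 90% power.

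- Independent observations per arm: [1.960·√(2·0.2·0.8) + 1.282·√(0.1·0.9 + 0.3·0.7)]² / 0.2² = (1.109 + 0.702)² / 0.04 ≈ 82.
- Design effect: 1 + (14 − 1)·0.10 = 2.3.
- Events per arm: 82·2.3/14 = 13.5, so 14 per arm and 28 in total.

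The stated 28 is reproduced and is not in dispute.

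**The test over 14 days.** For a logistic GEE with arm only and an independence working correlation, the estimate is the difference in logits of the two arm proportions. The robust variance in each arm is Σ(yᵢ − m·p̂)² / [n·m·p̂(1 − p̂)]², where yᵢ is the responder-day count of event i, m = 14 and n = 15. In this balanced layout Kauermann-Carroll multiplies the variance by n/(n − 1), and Mancl-DeRouen by its square. I simulated 200,000 null trials per setting (beta-binomial counts, 10% response in both arms).

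| 15 per arm, 14 days | Type I error |
|---|---|
| Robust, z, correlation 0.10 | 7.5% (7.7% with 14 per arm) |
| Robust, t(28), correlation 0.10 | 6.4% |
| Kauermann-Carroll, t(28), correlation 0.10 | 5.6% |
| Mancl-DeRouen, t(28), correlation 0.10 | 4.7–4.8% |
| Robust, z, correlation 0.3 / 0.5 (assumed) | 9.7% / 11.6% |
| Mancl-DeRouen, t(28), correlation 0.3 / 0.5 (assumed) | 6.6% / 8.5% |

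Failure to estimate is 0.0% at correlation 0.10 and 1.4% at 0.5. A group-by-day slope over 14 days, which is closer to the stated aim of faster improvement, gives 7.9% to 8.6% with the plain robust z test (2,000–3,000 runs).

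If patients were the clusters, the plain test would reject in 9.0–9.8% of trials with 15 patients of 2 episodes each, and in 10.7–12.9% with 10 patients of 3. These layouts are assumptions, because the article does not say how many patients will repeat.

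**The test over days 1–2.** The chance that one event has no response on either day is (1 − p)² + ρ·p(1 − p), with p = 0.10.

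- ρ = 0.10: 0.81 + 0.009 = 0.819. One arm empty: 0.819¹⁵ = 5.0%. At least one arm empty: 1 − 0.950² = 9.8%.
- ρ = 0.5 (assumed): 0.81 + 0.045 = 0.855. One arm empty: 0.855¹⁵ = 9.5%. At least one arm empty: 1 − 0.905² = 18.2%.

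Where the model can be fitted, the plain robust z test rejects in about 1.2–1.3% of null trials. Mancl-DeRouen with t rejects in under 0.5%, so the correction does not help in this window.

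**Power for 10% vs 30%, 14 days, correlation 0.10.** Plain robust z: 92.9% at 30 events and 91.3% at 28. Mancl-DeRouen with t: 88.9% and 86.2%.

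**The case against.** The strongest reply is that the article nowhere says the sandwich is uncorrected or that the reference is normal. The Blinding section refers to an analysis plan to be finalised before unblinding, and corrections, degrees of freedom and handling of empty arms are ordinary content for it. This stands in part. That the plain form will be used is an inference from silence. What is not silent is the choice of robust standard errors as the reason for using GEE, at a sample size where that choice needs a qualification.

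Four stronger readings are tempting, and the documents do not support them.

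- **One planned analysis both exceeds 5% and fails to run.** The two problems belong to different windows. Over 14 days at the planned correlation the model practically always fits. Over days 1–2, where it may not, the test is conservative. The non-finite estimate also presupposes a logit link, which the article does not state for the primary model.
- **Taking the episode as the unit inflates the error because episodes of one patient are correlated.** The unit is defined for allocation, and the article does not say what the GEE clusters on. Because each episode is randomised separately, simulations clustered on episodes showed no rise in error as within-patient correlation grew. Repeats are allowed, not certain, and must have a different focal location.
- **Later episodes are contaminated by earlier active stimulation.** That is a design question. The documents give no figure for it, and it does not bear on the standard errors.
- **The planned 28 events are wrong.** They follow from the stated inputs.

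**Conclusion.** The point holds as a cheap improvement, not as a demonstrated error in the final analysis. If the primary test is a plain robust z test over 14 days, its type I error at the protocol's own inputs is about 7.5% (7.7% at 28 events). It would be higher if the true correlation exceeds 0.10 or if patients rather than events are the clusters. Both of those are assumptions, and the conclusion does not depend on them. If the test is restricted to the two days on which sham is given, 5% is not delivered either: about 10% to 18% of null trials give no finite estimate on the logit scale, and the rest reject in about 1.3%.

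The figures rest on a two-sided 5% level, a logit link, an independence working correlation, equal arms and complete data.

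**What to change.** State the following before unblinding.

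- **Primary p-value:** a re-randomisation test of the randomised arm that follows the actual block list. It is valid in either window, with few responders and at any correlation. As a minimum alternative for a 14-day analysis, use a Mancl-DeRouen or Kauermann-Carroll corrected sandwich with a t reference. This should not be relied on for a two-day window, and it still exceeds 5% at higher correlations.
- **Interval:** from the corrected GEE, with the cluster unit named, and an exact interval for the risk difference if an arm has no responders.
- **Sensitivity analysis:** each patient's first episode only, in case some patients contribute more than one.

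The cost is a little programming and a wider interval. With Mancl-DeRouen and t(28), the logit-scale interval at 15 per arm widens by a factor of (15/14)·(2.048/1.960) ≈ 1.12. Power for the corrected t test is about 89% at 30 events and 86% at 28, slightly below the stated 90%, and should be reported as such.
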